## Abstract

**Introduction:**

Fu’s subcutaneous needling (FSN) is a new type of acupuncture that uses subcutaneous tissue to oscillate from side to side to improve muscle pathology status and can be effective in treating Knee osteoarthritis. Nonetheless, whether the clinical effect is similar to that of most commonly used drugs is unclear. Thus, this study aims to determine the pain-relieving effect and improvement in the joint function of the FSN therapy by comparing it with that of a positive control drug (celecoxib). Furthermore, this clinical trial also aims to evaluate the effect of FSN on gait and lower limb muscle flexibility, which can further explore the scientific mechanisms of the FSN therapy.

**Methods and analysis:**

This study is a randomized, parallel-controlled, single-center prospective clinical study that includes 60 participants, with an FSN group (n = 30) and a drug group (n = 30). The Fu’s subcutaneous needling (FSN) group undergo the FSN therapy 3 times a week for 2 weeks, while the drug group receives 0.2 g/day oral celecoxib for 2 weeks, with a follow-up period of 4 weeks after the completion of treatment. The primary outcome is the difference in the visual analog scale score after 2 weeks of treatment compared with baseline. The Western Ontario and McMaster Universities (WOMAC) Osteoarthritis Index, joint active range of motion test, three-dimensional gait analysis, and shear wave elastic imaging technology analysis in lower limb muscles are also performed to demonstrate clinical efficacy.

**Ethics and dissemination:**

The trial is performed following the Declaration of Helsinki. The study protocol and consent form have been approved by the Ethics Committee of Guangdong Provincial Hospital of Chinese Medicine. All patients will give informed consent before participation and the trial is initiated after approval. The results of this trial will be disseminated through publication in peer-reviewed journals.

*Trial registration number*: NCT06328153.

**Supplementary Information:**

The online version contains supplementary material available at 10.1186/s13018-024-04878-7.

## Introduction

Knee osteoarthritis (KOA) is one of the most common types of osteoarthritis, with clinical manifestations of knee pain, stiffness, and limited function, which in severe cases leads to bone deformity of the knee [1, 2]. Globally, nearly 30% of people over 45 years of age have imaging manifestations of KOA, and approximately half of them are symptomatic [3]. In China, the prevalence of symptomatic KOA requiring medical consultation is as high as 8.1% [4]. Apparently, KOA poses a considerable burden to both patients and the national healthcare system. Age is an essential risk factor for the development of KOA, and the incidence increases with age and peaks in the elderly population after the age of 65 years [5, 6]. The pathogenesis of the disease is currently thought to be mainly related to abnormal mechanical factors, including abnormal joint mechanics, muscle dysfunction, gait abnormalities, and disturbances in bone alignment, which lead to biochemically mediated biological effects [7, 8].

Studies have shown that abnormal skeletal muscle function in the lower limbs, especially weakening of the quadriceps, increases the load on the knee joint, which is closely related to this disease [9]. Skeletal muscles can absorb loads. In normal physiology, the biomechanical effect of the muscles around the knee joint on the joint is in balance with the external loads acting on the knee joint as a whole, whereas in the pathological state, due to the dysfunction of the muscles, the mechanical loads acting on the knee joint are in a state of imbalance, which leads to an abnormal patellar movement trajectory. With a decrease in the stability of the joint, it provokes or exacerbates inflammatory pathology of the articular cartilage and dysfunction of the knee joint [9–12]. Lower limb muscle weakness has been reported to precede the onset of joint pain and imaging changes in patients with senile knee osteoarthritis, and diminished muscle strength is positively correlated with disease severity [13, 14]. It was also found that by improving the mechanical properties of the lower limb muscle, the knee adduction moment (KAM) and medial compartmental pressure of the knee could be reduced, thus counteracting the abnormal external loads acting on the knee joint and ultimately achieving a therapeutic effect on KOA [10]. It is clear that improving the condition of the relevant lower limb muscles, especially the quadriceps, may play an important role in the prevention and treatment of senile knee osteoarthritis.

Currently, acupuncture has been increasingly used in the practice of KOA treatment, effectively relieving the symptoms of pain and joint stiffness [15, 16]. A large-sample, multicentre study found that electroacupuncture treatment for KOA achieved a response rate of 60.3% at Week 1, and demonstrated satisfactory long-term effects at Week 26 [17]. Fu’s subcutaneous needling (FSN) is an emerging acupuncture modality, characterized as safe, eco-friendly and efficient. It has been used in clinical practice for more than 20 years. The practitioner uses a specially designed needle to perform horizontal reciprocal swaying within loose connective tissues under the skin, in conjunction with the Reperfusion Approach. FSN therapy is distinguished by its rapid onset of effect [18]. A meta-analysis showed that FSN significantly treated KOA and had a faster onset of effect than did manual acupuncture, drugs, and herbal medicine [19]. The only target objects for FSN are muscles under pathological tension. It has been demonstrated that the reciprocal Swaying Movement of the FSN in the loose connective tissue and the Reperfusion Approach of muscle contraction-diastole elevate the perfusion of vascular blood flow through the interosseous space [20]. This restores healthy muscle elasticity [21] and further restores joint stability of the knee, thereby having a therapeutic effect on KOA. We hypothesized that this is the reason why FSN is effective.

Our preliminary study revealed that the modulus of elasticity of the lateral femoral muscle was significantly higher on the affected side than on the healthy side in patients with KOA (*p* < 0.01). It was also found that FSN significantly improved symptoms and signs while reducing the modulus of elasticity of the lower limb skeletal muscles (vastus lateralis, tibialis anterior, and gastrocnemius) of KOA patients (*p* < 0.05), and a related paper is being prepared for publication. Previously, two studies have suggested that FSN therapy applied for the treatment of KOA effectively relieved pain [22, 23]. However, both studies only applied pain-related measures or function-related measures as indicators of efficacy. Few studies have focused on a biomechanical point of view. There are also few published clinical studies that have used objective measures other than scales, such as ultrasonography or imaging. Therefore, the objective of this randomized clinical trial is to investigate the clinical effects and biomechanical mechanisms of FSN for the treatment of elderly patients with knee osteoarthritis. We hypothesized that an intervention programme using FSN for 2 weeks, 3 times per week, would produce better improvements in pain as well as physical function of the knee compared to a positive control group taking celecoxib. Furthermore, this clinical trial also aims to evaluate the ability of FSN to improve gait and lower limb muscle flexibility, which may further help explore the mechanism of FSN therapy.

## Method and analyses

### Study design

The study will be conducted from May 2024 to March 2026 at Guangdong Provincial Hospital of Chinese Medicine and will be performed according to the Declaration of Helsinki.

This is a randomized controlled, parallel, single-center prospective clinical trial. The study has been approved by the Ethics Committee of Guangdong Provincial Hospital of Chinese Medicine (Ethics registration ID: BF2022-101-01) and was registered on the clinical trial platform (ClinicalTrials.gov ID: NCT06328153; Protocol ID: BF2022-101).

### Study setting

Participants are recruited from the outpatient department of Guangdong Provincial Hospital of Chinese Medicine. Eligible and consented participants are randomly assigned at a ratio of 1:1 to receive treatment in the FSN group (n = 30) or drug group (n = 30) for 2 weeks. Participants are assessed at baseline and on the 7th, 14th, 28th, and 42nd days after the start of the intervention. The design of the trial is summarized in Fig. 1.

**Fig. 1 Fig1:**
[figure not shown]
Planned study protocol flowchart

### Participants

#### Inclusion criteria

Participants who meet the diagnostic criteria for KOA according to the Guidelines for the Diagnosis and Treatment of Osteoarthritis (2018 Edition) by Osteoporosis Group of the Chinese Orthopaedic Associationg [24] and the diagnostic criteria for KOA formulated by the American College of Rheumatology [25] are eligible to participate when they also meet the following criteria:The patients are aged between 60 and 80 years.BMI < 28.Kellgren–Lawrence grade 1–3.Knee pain score > 3 on a 10-point numerical rating scale (VAS).Voluntary and capable of signing the informed consent form.

#### Exclusion criteria

Non-primary knee osteoarthritis, such as gouty arthritis and traumatic arthritis.According to the above guidelines, the affected knee severely deformed, either clinically or radiologically.Patients who have taken analgesics or Non-steroidal Anti-Inflammatory Agents (NSAIDs) orally or topically on the affected knee within the last month; who have received adjuvant treatment for the affected knee joint (e.g., physical therapy, acupuncture, massage, etc.) within the last 3 months; or who have a history of knee surgery in the past 6 months.With other diseases that may cause lower limb pain, such as lumbar disc herniation and lumbar spinal stenosis.With lower extremity vascular diseases.With Severe systemic or lower limb local skin diseases.With any unstable medical disease (e.g., acute cardiac or cerebrovascular disease, poorly controlled diabetes, etc.) or psychiatric illness.With contraindications to NSAIDs, which include postcoronary artery bypass graft surgery, active peptic ulcer, severe heart failure, etc.

### Sample size calculation

The main outcome measure of this study is the decrease in VAS score from baseline during the 2-week treatment period. FSN, an emerging acupuncture method, has been studied in randomized controlled trials [22, 23]. However, both of these previous studies used superiority testing, which cannot provide an appropriate reference for the sample size calculation of our study. Therefore, we refer to a randomized controlled trial that compared electroacupuncture with an NSAID for treating KOA [26]. We assume that the effect sizes of interventions (FSN and celecoxib) in this trial were similar to those (acupuncture and diclofenac applied for interventions) in the aforementioned study. The results of the above study showed that the VAS score decreased by 48.24 ± 3.59 mm from baseline after 4 weeks of electroacupuncture treatment, and by 32.99 ± 3.94 mm from baseline after 4 weeks of oral administration of diclofenac. The actual difference in the VAS score between the two interventions after 4 weeks of treatment was 15.25 mm, with a combined standard deviation of 3.85 mm. However, since the course of treatment in our trial is half of that in the aforementioned study, appropriate adjustments for the expected difference in the VAS score are needed. Based on our clinical experience, the efficacy and the treatment period cannot be considered to increase in full equivalence, and since the 2-weeks intervention course is relatively short, we would not expect the cumulative efficacy to be half that of the 4-weeks intervention in the aforementioned study.

Therefore, to compare the efficacy of FSN and celecoxib, we assume that the difference in two groups’ means of the changes in the VAS score is 6.5 mm after 2 weeks of treatment, which is slightly less than half the difference observed in the reference trial [26] after 4 weeks of intervention. Assuming a 1:1 ratio of participants in the 2 groups, the NIM (Non-Inferiority Margin) is defined as 10 mm. A two-sided test with a significance level (α) of 0.05 and a power(1-β) of 0.80 is applied. With a possible dropout rate of 10%, using the PASS 15.0 software, 60 participants shall be included in this study.

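### The only planning SD, 3.85 mm, is implausibly small for patient-level VAS change; at realistic SDs, 27 per arm falls well short of 80% power to show the hypothesised 6.5 mm benefit

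*Protocol article*

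**What the plan says.** The protocol article's section on sample size calculation borrows from a trial of electroacupuncture against diclofenac. It reports that "the VAS score decreased by 48.24 ± 3.59 mm from baseline after 4 weeks of electroacupuncture treatment". The corresponding figure for the diclofenac arm is 32.99 ± 3.94 mm. The section puts the difference at 15.25 mm, "with a combined standard deviation of 3.85 mm". No other SD appears, and the cited trial's arm sizes are not given. The section then assumes that the difference between groups in "means of the changes in the VAS score is 6.5 mm after 2 weeks of treatment", sets a non-inferiority margin of 10 mm, and adds: "A two-sided test with a significance level (α) of 0.05 and a power(1-β) of 0.80 is applied". With 10% dropout it arrives at 60 participants.

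Elsewhere the aim is superiority. The Introduction hypothesises that FSN "would produce better improvements in pain as well as physical function of the knee compared to a positive control group taking celecoxib", the Conclusion repeats this, and the Statistical analysis section plans two-sided difference tests at P < 0.05. The primary outcome is the change from baseline to day 14 on a 0 to 100 mm line that the participant marks.

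**The concern.** A sample size for a comparison of mean changes needs the spread of change between patients. A spread below 4 mm on a self-marked 100 mm pain line would mean that nearly everyone in an arm improves by almost the same amount. Figures of this size are more often seen as the precision of a mean than as the spread of individuals.

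If the true SD is several times larger, the trial is much less able to show the benefit it hypothesises than its 80% figure suggests. A non-significant result could then be read as evidence of no difference when it is merely imprecise.

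**Working it through.** **Inputs, all from the sample size section:** changes of 48.24 ± 3.59 and 32.99 ± 3.94 mm; difference 15.25 mm; SD 3.85 mm; assumed difference 6.5 mm; margin 10 mm; two-sided α 0.05 (one-sided 0.025 for non-inferiority); power 0.80; dropout 10%; total 60. Evaluable per arm: 30 × 0.9 = 27.

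**1. The plan's own figure.** Smallest n per arm from the noncentral t distribution at SD 3.85 and 80% power, divided by 0.9 and rounded up:

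| Reading | Distance (mm) | n per arm | Total with dropout |
|---|---|---|---|
| Superiority | 6.5 | 7 | 16 |
| Non-inferiority, no true difference | 10 | 4 | 10 |
| Non-inferiority, FSN 6.5 mm better | 10 + 6.5 = 16.5 | 3 | 8 |
| Non-inferiority, 6.5 mm taken off the margin | 10 − 6.5 = 3.5 | 21 | 48 |

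None gives 60. The last reading does reach it at 90% power: 27 per arm, 27/0.9 = 30, total 60. The text states 80%.

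**2. Is 3.85 mm credible as a patient-level SD?**
- Standardised difference in the cited trial: 15.25/3.85 = 3.96 SD. The planned 6.5 mm would be 6.5/3.85 = 1.69 SD.
- 95% range of change, electroacupuncture: 48.24 ± 1.96 × 3.59 = 41.2 to 55.3 mm.
- 95% range of change, diclofenac: 32.99 ± 1.96 × 3.94 = 25.3 to 40.7 mm.

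The ranges do not overlap: almost every electroacupuncture patient would have improved more than almost every diclofenac patient.

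**3. If 3.85 were a standard error,** SD = 3.85 × √n. For assumed arm sizes of 15, 30 and 60 this gives 14.9, 21.1 and 29.8 mm.

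**4. Power with 27 per arm.** Standard error of the difference = SD × √(2/27); noncentrality = distance / standard error; 52 degrees of freedom; critical value 2.007. The confidence interval half-width is 2.007 × SD × √(2/27); for example, 2.007 × 15 × 0.2722 = 8.2 mm. The SDs of 10 to 25 mm are assumptions, because the article gives no usable value.

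| Assumed SD (mm) | Superiority, 6.5 mm | Non-inferiority, no true difference | Non-inferiority, FSN 6.5 mm better | 95% CI half-width (mm) |
|---|---|---|---|---|
| 10 | 65% | 95% | about 100% | 5.5 |
| 15 | 35% | 67% | 98% | 8.2 |
| 20 | 22% | 44% | 85% | 10.9 |
| 25 | 15% | 30% | 66% | 13.7 |

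Superiority power is 80% at an SD of about 8.4 mm. With all 30 per arm evaluable it is still only 38% at SD 15 and 24% at SD 20.

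**The case against.** The strongest reply is that the 80% may not be a superiority claim. The sample size section sets aside two earlier FSN trials because they tested superiority, and it then defines a 10 mm margin. On its own scenario, FSN 6.5 mm better and tested against that margin, power is 98% at SD 15 and 85% at SD 20. This stands. A reader might infer that the trial is underpowered on every reading, and the figures do not support that. What remains is that the hypothesis and the planned tests are those of superiority, and the section does not say which aim its power serves.

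A reader might also infer that the ± values are certainly standard errors. The article cannot show this. The conversions above rest on assumed arm sizes. Equal weighting of 3.59 and 3.94 gives √((3.59² + 3.94²)/2) = 3.77, so 3.85 needs about 73% of the weight on diclofenac, which points to unequal arms that are not described. The entry criterion does not settle it either. It has a lower pain limit ("Knee pain score > 3 on a 10-point numerical rating scale (VAS") and no upper one, so a patient entering at 35 mm could not fall by 41 mm. But the cited falls came after 4 weeks in another trial, whose entry rules are not shown. This makes the transfer of the SD to this trial doubtful; it does not identify the cited figures as standard errors.

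A third tempting inference is that 60 participants reveal a hidden SD near 21 mm, since that SD gives about 80% power over 16.5 mm with 27 per arm. The route is not unique: SD 3.85 with a 3.5 mm distance and 90% power also gives 60. The total is therefore no evidence for either SD.

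**Conclusion.** The concern holds in a limited form. As a between-patient SD of VAS change, 3.85 mm is unjustified and implausibly small on the article's own figures. That conclusion does not require the ± values to be standard errors.

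Power to show 6.5 mm falls short of 80% once the true SD exceeds about 8.4 mm, and is 15% to 35% at assumed SDs of 25 down to 15 mm. Non-inferiority with no true difference is also short of 80% at SDs of 15 mm or more (67% down to 30%). If FSN truly is 6.5 mm better, non-inferiority power stays above 80% up to an SD of about 21 mm.

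Separately, 60 does not follow from the stated inputs at 80% power on any reading tried. The calculations assume equal SDs, 27 evaluable per arm and an unadjusted comparison of mean changes.

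**What to change.** 1. Check in the cited trial whether ± denotes SD or standard error, and report its arm sizes.
2. Replace 3.85 mm with a justified patient-level SD of 2-week VAS change, taken from that trial, from the preliminary FSN data that the Introduction mentions, or from a blinded pooled SD of participants already enrolled.
3. State whether the 80% power refers to superiority or to non-inferiority, and which true difference it assumes.
4. Keep 60 participants, and restate the power and the expected 95% confidence interval half-width that 27 per arm gives (about 8.2 mm at SD 15, 10.9 mm at SD 20).
5. Interpret the confidence interval against 0 and against the 10 mm margin. A rule that calls any interval containing both 0 and 6.5 mm inconclusive should not be used: at SD 20 an estimate of 6.5 mm gives −4.4 to 17.4 mm, which contains both values yet excludes a deficit of 10 mm.

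The cost is a look-up, possibly a blinded variance estimate, and a rewritten paragraph. No extra participants are needed, but the stated power becomes less favourable.

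### The sample size of 60, the power of 0.80 and the other inputs printed with them are mutually inconsistent, so at least one is misreported

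*Protocol article*

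**What the plan says.** All the inputs stand in one section of the protocol article, Sample size calculation.

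- **Expected difference:** the group difference in "means of the changes in the VAS score is 6.5 mm after 2 weeks of treatment". No sign is attached. It is derived from a reference trial of electroacupuncture against diclofenac, in which VAS fell by 48.24 mm and 32.99 mm, a gap of 15.25 mm in favour of needling. The 6.5 mm is described as a figure "which is slightly less than half the difference observed in the reference trial".
- **SD:** 3.85 mm, presented as the combined SD of that trial, whose arms had 3.59 and 3.94 mm.
- **Margin:** "the NIM (Non-Inferiority Margin) is defined as 10 mm".
- **Alpha:** "A two-sided test with a significance level (α) of 0.05".
- **Power:** "a power(1-β) of 0.80 is applied".
- **Allocation and dropout:** 1:1 and 10%.
- **Result:** "using the PASS 15.0 software, 60 participants shall be included in this study", that is 30 per arm, or 27 per arm after 10% dropout.

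On direction, the Introduction hypothesises that FSN "would produce better improvements in pain as well as physical function of the knee compared to a positive control group taking celecoxib", and the Conclusion likewise expects FSN to do better than celecoxib.

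**The concern.** A sample size statement should let a reader put the printed inputs into the named test and recover the printed number. This one does not. It sets a non-inferiority margin but also an expected difference that, by its source and by the trial's hypothesis, favours the new treatment. The further the truth is expected to lie on the favourable side, the fewer participants a non-inferiority test needs, so a 10 mm margin and a 6.5 mm benefit against an SD of 3.85 mm should call for very few.

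The sample size and power are figures that the trial relies on. The article commits to CONSORT reporting, so this justification can be expected to go into the results paper. A reader who recomputes it will not get 60, and will not be able to tell what the trial was sized to show.

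**Working it through.** **Inputs** (all from Sample size calculation): difference 6.5 mm, SD 3.85 mm, margin 10 mm, two-sided alpha 0.05 (0.025 for the one-sided non-inferiority bound), power 0.80, 1:1, dropout 10%.

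**Formula.** Let D be the distance between the assumed true difference and the value being tested against. The normal approximation per arm is n = 2 × [SD × (z₀.₉₇₅ + z₀.₈₀) / D]². With z₀.₉₇₅ + z₀.₈₀ = 1.960 + 0.842 = 2.802, this is about 232.7 / D². The exact version takes the smallest n at which the two-sample non-central t test reaches the required power. Dropout: divide n per arm by 0.9, round up, and double.

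**Attempt to reproduce 60 at power 0.80:**

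| Use of the 6.5 mm | D (mm) | n/arm, normal | n/arm, t | Total with dropout (t) |
|---|---|---|---|---|
| Non-inferiority, FSN benefit | 10 + 6.5 = 16.5 | 1 | 3 | 8 |
| Non-inferiority, no true difference | 10 | 3 | 4 | 10 |
| Superiority | 6.5 | 6 | 7 | 16 |
| Non-inferiority, FSN deficit | 10 − 6.5 = 3.5 | 19 | 21 | 48 |

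For example, in the last row 232.7 / 3.5² = 18.99, so 19. The t test needs 21 (power 0.820), since 20 per arm falls just short of 0.80. Then 21 / 0.9 = 23.3, so 24 per arm and 48 in total. Adding 10% instead of dividing by 0.9 also gives 48. No row gives 60.

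**Power at 27 evaluable per arm.** The standard error is 3.85 × √(2/27) = 1.048 mm.

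- Deficit: 3.5 / 1.048 = 3.34 standard errors, power 0.906.
- Superiority: 6.5 / 1.048 = 6.20, power above 0.999.
- No true difference: 10 / 1.048 = 9.54, power above 0.999.
- Benefit: 16.5 / 1.048 = 15.75, power above 0.999.

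None is 0.80.

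**Settings that do give 60:**

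- Deficit (D = 3.5), SD 3.85, one-sided 0.025, power **0.90**: 27 per arm by t test (26 gives 0.895, 27 gives 0.906). 27 / 0.9 = 30 per arm, 60 in total. The only departure from the printed inputs is the power, given the deficit sign.
- Deficit, SD 3.85, **one-sided 0.05, power 0.95**: also 27 per arm, so 60.
- Deficit, one-sided 0.025, power 0.80, **SD about 4.5 mm**: 27 per arm (power 0.801), so 60.
- At power 0.80 and one-sided 0.025, an SD of about 8.3 mm (superiority), 12.7 mm (no true difference) or 21 mm (benefit) would also give 27 per arm.

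**Direction.** The source difference favoured needling (48.24 − 32.99 = 15.25 mm), and half of it is 7.6 mm, so 6.5 mm as slightly less than half is a benefit of FSN. Entering it as a deficit would contradict both that source and the hypothesis in the Introduction and Conclusion.

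**The SD.** Equal weighting of 3.59 and 3.94 gives √[(3.59² + 3.94²)/2] = 3.77 mm. A combined value of 3.85 needs weights of about 27:73. The reference trial's arm sizes are not given, so 3.85 cannot be confirmed or refuted.

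**The case against.** The best defence is that the calculation is conservative: every reading of the printed inputs needs fewer than 60, and 60 may simply have been rounded up. The first half stands. On the stated inputs there is no shortfall in power. The second half is weak, because the section presents 60 as what the software returned after allowing for dropout, and the reading that fits the hypothesis gives 8.

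A second defence is that the entries made in the software are not shown, so the cause of the mismatch is unknown. This also stands, and it limits what can be said. Because the deficit reading at power 0.90 lands exactly on 60, a reader might infer that this is how 60 was obtained, that the sign was reversed and that the stated 0.80 is the wrong figure. The documents do not support that as fact. The 6.5 mm carries no sign, no 3.5 mm distance is printed, and different values of alpha and power, or of the SD, reach 60 as well.

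A reader might also infer that 3.85 mm is a pooling mistake because equal arms give 3.77. That does not follow either, since unequal arms could produce it.

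**Conclusion.** Wrong as written. N = 60, power 0.80 and the other printed inputs cannot all be true together. The stated inputs give 8, 10, 16 or 48, and 27 evaluable per arm gives power of 0.906 or above 0.999. At least one printed figure is misreported, and the documents do not show which. The exact match under a deficit with power 0.90 is a plausible lead for the authors to check, not a finding.

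These figures assume a two-sample t test, one-sided 0.025 for the non-inferiority bound, SD 3.85 mm and 10% dropout. The power figures depend heavily on that SD. The consequence is an irreproducible justification that does not show whether 60 was sized for non-inferiority or superiority; it is not evidence that the trial is too small on its own inputs.

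**What to change.** Keep 60 and rewrite the paragraph:

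1. Name the test that the sample size is for.
2. Give the sign of the 6.5 mm and the resulting distance to the margin.
3. State the alpha (and sidedness), SD and power actually entered in PASS, and correct whichever printed value differs from them.
4. Say how the 3.85 mm was combined from the two arm SDs.
5. Restate the power that 27 evaluable per arm gives under the corrected inputs, for non-inferiority and separately for superiority, naming the SD on which each depends.

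The cost is one reworded paragraph after checking the saved software entries. Enrolment does not change.
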